## Inclusion and exclusion criteria

Eligibility depends on clinical and staging requirements, summarized in Box 1.

**Box 1.** Inclusion and exclusion criteria.

**Table Taba:** 

Inclusion Criteria	Exclusion Criteria
Patients diagnosed with malignant tumors in the head and neck region	Previous radiation therapy to the head and neck region
Who will start RT or CRT	Severe or uncontrolled periodontal disease
Both genders	Patients undergoing topical oral anti-inflammatory medication therapy (e.g., Omcilon-A Orabase^®^ [triamcinolone acetonide])
Ages 18 and older	
Informed Consent Form (ICF) signed	

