## Introduction

Head and neck cancer (HNC) encompasses a broad category of various tumor types; approximately 40% of these occur in the oral cavity, 15% in the pharynx, 25% in the larynx, and 20% in other anatomical locations [1, 2]. According to GLOBOCAN data, it is estimated that more than 1.2 million new cases of head and neck cancer will be diagnosed worldwide by 2040 [3].

Antineoplastic treatment (AT) for patients with HNC includes surgical techniques, chemotherapy (CT), radiation therapy (RT), or combination therapy, administered according to the tumor stage and location [4, 5]. For patients with early-stage squamous cell carcinoma, both surgery and radiation therapy yield comparable results in terms of local disease control and overall survival. Following surgery, postoperative radiotherapy, with or without adjuvant chemotherapy, is recommended for patients with pathological risk factors, including perineural invasion, lymphovascular invasion, and positive or narrowly clear surgical margins [6]. RT is an important therapeutic modality for the treatment and control of HNC, as it allows for tumor eradication while preserving the function of normal tissues in the affected region [7], and is used as part of a curative treatment regimen for 75% of patients with head and neck squamous cell carcinoma (HNSCC) [8].

The total radiation dose for curative-intent treatment depends on tumor location and type, typically ranging from 50 to 70 Gy in conventional radiotherapy regimens. In most cases, this dose is delivered in fractions of 1.8 to 2.0 Gy per day, five days a week, over a period of five to seven weeks [9].

Side effects may occur with these treatments; in the oral cavity, the acute effects of RT include oral mucositis, changes in saliva viscosity and volume, dysgeusia, candidiasis, and limited mobility [5]. Chronic effects include neuropathy, atrophy of the facial muscles and salivary glands, halitosis, dysphagia, dysphonia, osteoradionecrosis, xerostomia, hyposalivation, dental caries, and periodontal disease [5].

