## Sample size

The sample size was determined based on a non-inferiority design, assuming that transcutaneous infrared PBMT would demonstrate clinical efficacy comparable to intraoral red PBMT in the prevention of OM. The non-inferiority margin was defined as Δ = 0.5 points on the WHO scale, based on the differences observed between CT and IO protocols in direct comparative studies [25, 26]. Calculations were performed using the ClinCalc platform to compare two independent means, assuming a significance level (α) of 0.025 (one-tailed test) and a statistical power (1 - β) of 80%. To account for a predicted 10% attrition rate (dropouts), the final sample size was established at 54 participants (*n* = 27 per group). Participants will be recruited through consecutive sampling to ensure a representative flow of patients at the study site.

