## Clinical and treatment-related variables

Prophylactic PBMT will be administered thrice weekly during radiation therapy. Following institutional standards, all patients will undergo intensity-modulated radiation therapy (IMRT). The prescribed radiation regimen consists of total doses ranging from 60 to 70 Gy, delivered in 30 to 35 fractions of 2 Gy (200 cGy) per fraction, five days a week.

Following a pragmatic design, patients on concurrent chemotherapy will be included. As chemotherapy significantly impacts OM risk, it will be recorded and treated as a covariate in multivariable regression analyses to adjust for potential confounding on outcomes.

The standardized PBMT schedule was set for Monday, Wednesday, and Friday during all weeks of RT, ensuring a maximum interval of two days between sessions and coverage of at least three consecutive RT fractions. Three times per week (rather than daily) was based on the operational feasibility of the referral oncology service (patient flow and researcher availability), evidence from randomized clinical trials demonstrating that the efficacy of three-times-weekly PBMT protocols is comparable to daily frequency in SCC populations [22], and protocols approved by the MASCC/ISOO guidelines that include alternate frequencies [17].

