### Statistical analysis

Analyses will be performed using Jamovi software (version 2.6.44). Normality will be assessed using the Shapiro-Wilk test, and variables will be described using frequencies and percentages (categorical variables) or means, standard deviations, and medians with interquartile ranges (continuous variables). Baseline comparability between groups will be assessed using Student’s t-test or the Mann-Whitney U test (continuous variables) and the chi-square test or Fisher’s exact test (categorical variables).

The primary outcome, oral mucositis severity (WHO scale), will be analyzed longitudinally using a mixed-effects ordinal logistic regression model to account for the repeated measurements. The model will include treatment group, assessment time, and the treatment vs. time interaction as fixed effects, with participant included as a random effect to account for within-subject correlation. Total radiotherapy dose, tumor location, and concomitant chemotherapy will be included as covariates.

Pain intensity (NRS) will be analyzed longitudinally using an appropriate mixed-effects regression model according to its distribution. The primary analysis will follow the intention-to-treat principle. Missing outcome data will not be imputed; instead, the mixed-effects ordinal logistic regression model will incorporate all available repeated measurements and account for incomplete observations over time under the assumption that data are missing at random.

The primary objective is to determine whether transcutaneous infrared PBMT is non-inferior to intraoral red PBMT regarding oral mucositis severity. Non-inferiority will be assessed using the estimated treatment effect obtained from the longitudinal mixed-effects model and interpreted according to the prespecified non-inferiority margin of 0.5 WHO grade.

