Recent literature comparing IO and TC PBMT confirms that while both modalities are clinically effective for the prevention and management of OM, they exhibit distinct optical delivery profiles and impact the patient experience differently. A critical consideration in PBMT is that light intensity attenuates exponentially as it traverses biological tissue. Consequently, the intraoral route offers a direct advantage by delivering photons directly to the target irradiated mucosa. In contrast, the efficacy of the transcutaneous route is highly dependent on the optimization of laser parameters, specifically wavelength (favoring the “optical window” of near-infrared), irradiance, and exposure time to ensure that a sufficient therapeutic dose reaches the deeper mucosal layers [25, 42, 43]. Trials in hematopoietic stem cell transplantation and animal models reinforce that intraoral PBMT tends to promote a more localized effect and faster healing, although transcutaneous PBMT also contributes to epithelial recovery when used with appropriate parameters [42, 43].

On the other hand, Multicenter clinical trials in head and neck cancer and pediatric populations indicate that transcutaneous protocols may be as effective as intraoral ones in reducing the incidence, severity, and duration of OM, with no significant differences in the time to onset of ulcerated lesions or in overall mucositis scores [25, 42, 43, 44, 26]. In a randomized study of oral cavity and oropharyngeal carcinoma, transcutaneous PBMT using an 810/980 nm superpulsed laser demonstrated efficacy equivalent to intraoral PBMT across all grades of mucositis, with some additional functional benefits, such as reduced difficulty swallowing and less loss of taste at critical points in treatment [25, 26]. Similar results were reported in pediatric oncology patients, in whom transcutaneous PBMT was considered comparable to intraoral PBMT in terms of OM severity, duration of lesions, and functional impact, with a slight difference in pain at only one follow-up point [44].

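### Box 1 does not require oral or oropharyngeal mucosa in the planned radiation volume, so low-risk patients can dilute a true transcutaneous deficit against the fixed 0.5-grade margin

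*Protocol article*

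**What the plan says.** - **Eligibility.** The section on inclusion and exclusion criteria states "Eligibility depends on clinical and staging requirements, summarized in Box 1". The tumour and treatment criteria in Box 1 are "Patients diagnosed with malignant tumors in the head and neck region" and "Who will start RT or CRT". The others are sex, age and consent. The exclusions are previous head and neck radiotherapy, severe periodontal disease and topical oral anti-inflammatory drugs. None concerns tumour sub-site, treated volume or dose to the mouth.
- **Radiotherapy.** The section on clinical and treatment-related variables says all patients have IMRT, with "total doses ranging from 60 to 70 Gy, delivered in 30 to 35 fractions". This fixes the prescription but not what is irradiated.
- **Case mix and risk.** The Introduction describes head and neck cancer in general: "approximately 40% of these occur in the oral cavity, 15% in the pharynx, 25% in the larynx, and 20% in other anatomical locations". It also puts OM at 75% to 90% of patients treated for head and neck malignancies.
- **Test.** The sample size section sets a margin of 0.5 WHO grade, one-sided alpha 0.025, 80% power, 10% attrition and 27 patients per group. Randomisation is simple and unstratified. The primary analysis is by intention to treat, with a mixed-effects ordinal logistic model. "Total radiotherapy dose, tumor location, and concomitant chemotherapy will be included as covariates"; the only interaction named is treatment by time.

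**The concern.** The outcome can separate the two lasers only in patients whose oral or oropharyngeal mucosa receives a relevant dose. A patient whose plan largely spares the mouth tends towards low WHO grades in either arm. In a superiority trial such patients make the test conservative. Against a fixed absolute non-inferiority margin they do the opposite when TC is truly worse: the average deficit over all randomised patients is smaller than the deficit in the patients the conclusion is about.

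The planned safeguards do not remove this. Tumour location is a proxy for oral dose and enters only as a main effect. Total dose is the prescription, not the dose to the oral mucosa. The per-protocol set is defined by attendance at 80% of PBMT sessions, not by being at risk.

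A TC deficit is not far-fetched on the protocol's own account. It reports a 10- to 50-fold loss of fluence through tissue and leaves the soft palate out of the TC points.

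**Working it through.** **1. The plan's own figure.** No SD is stated, so 27 per group cannot be reproduced directly. Solving backwards:

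n per arm = 2 × (1.960 + 0.842)² × SD² / 0.5²

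With SD = 0.61 this is 2 × 7.85 × 0.372 / 0.25 = 23.4, so 24; and 24 / 0.9 = 26.7, so 27. The stated size therefore implies an SD near 0.61 and about 24 evaluable patients per arm. The missing SD is a separate matter; it is back-solved here only to set the scale.

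**2. Range for f.** The complement of 75-90% is 10-25%. Part of that complement is at-risk patients who escape OM, so it serves as a rough ceiling on f.

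**3. Model.** A share f sits at grade 0 in both arms. The rest have IO mean μ and TC mean μ + 0.5, with common SD s. Assumed ranges: s = 0.62 to 1.0, μ = 1.5 to 2.0, 24 per arm.

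- Whole-trial difference: d = (1-f) × 0.5
- Variance, IO arm: (1-f)s² + f(1-f)μ²; TC arm: the same with μ + 0.5 in place of μ
- SE = √[(sum of the two variances)/24]
- P(declare non-inferiority) = Φ[(0.5 - d)/SE - 1.96]
- If location adjustment removes the between-group variance: SE = √[2(1-f)s²/24]

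**4. Worked case, f = 25%, s = 0.62, μ = 1.5.** d = 0.375. The variances are 0.288 + 0.422 = 0.710 and 0.288 + 0.750 = 1.038. SE = √(1.748/24) = 0.270. Φ(0.125/0.270 - 1.96) = Φ(-1.50) = 6.7%. With the extra variance removed, SE = 0.155 and Φ(0.125/0.155 - 1.96) = Φ(-1.15) = 12.4%.

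**5. Over the assumed ranges**

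| f | Whole-trial difference when the at-risk deficit is 0.5 | At-risk deficit that shows as 0.5, i.e. 0.5/(1-f) | False non-inferiority, extra variance kept | False non-inferiority, extra variance removed |
|---|---|---|---|---|
| 0 | 0.500 | 0.50 | 2.5% | 2.5% |
| 10% | 0.450 | 0.56 | 3.5-4.1% | 3.8-4.8% |
| 20% | 0.400 | 0.63 | 4.6-5.8% | 5.8-9.1% |
| 25% | 0.375 | 0.67 | 5.2-6.7% | 7.2-12.4% |

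**6. If the arms are truly equal.** At s = 0.62, power with the extra variance kept falls from 80% (f = 0) to 54-65% at f = 10% and 40-54% at f = 25%. For f = 25%, μ = 1.5: SE = √(2 × 0.710/24) = 0.243, and Φ(0.5/0.243 - 1.96) = Φ(0.095) = 54%.

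**The case against.** - **The article is a condensation.** Box 1 is introduced as a summary that includes staging requirements, yet it lists none, so it may be abbreviated and a fuller document may hold a site or field criterion. That limits certainty about the trial. It does not change what the published criteria permit.
- **The arithmetic is for means, not for the planned model.** Patients always at grade 0 carry little information on a conditional odds ratio, and location adjustment may limit dilution of it. This stands as a caveat on the figures. The margin, however, is in WHO grades, and a grade difference averaged over all participants is diluted again.
- **Broad eligibility suits a pragmatic pilot at one centre.** That is a fair preference, but the article also states a confirmatory-style non-inferiority test, for which the population matters.

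A reader might also infer more than the documents support:

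- That the low-risk patients cannot develop OM. Nothing says so; some fields outside the oral cavity reach oral mucosa, and the protocol itself says chemotherapy raises OM risk.
- That f could reach 45% by adding larynx and other sites. Those percentages describe head and neck cancer in general, not this centre's patients, and 45% without OM risk sits badly with an incidence of 75-90%.
- That short or low-dose courses slip through Box 1. The regimen is already stated for all patients elsewhere in the article.
- That the margin comes from a different population. The sample size section says it is "based on the differences observed between CT and IO protocols in direct comparative studies", and the Discussion cites the same references for one trial, "In a randomized study of oral cavity and oropharyngeal carcinoma". It also lists them among wider head and neck and paediatric trials, so their populations cannot be settled from the article.

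**Conclusion.** The point holds in a limited form. As published, eligibility does not tie enrolment to irradiation of the mucosa on which the outcome is measured, and nothing in the analysis restores the comparison on the grade scale. With f at most about 10-25%, and TC exactly 0.5 grade worse in at-risk patients, the false non-inferiority rate is roughly 3.5-7% against a nominal 2.5%, or up to about 12% if location adjustment removes the extra variance.

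The direction is conditional: these patients ease a non-inferiority claim only when TC is truly worse, and cost power when the arms are equal. The size rests on an assumed f, an assumed at-risk mean and SD, grade 0 for all low-risk patients, and a normal approximation to a difference in means. This is a cheap improvement, not a reason to halt the trial.

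**What to change.** 1. **Patients still to be enrolled.** Add to Box 1 that the planned IMRT volume includes oral cavity or oropharyngeal mucosa, checked on the plan before randomisation.
2. **All patients.** Record planned oral-mucosa involvement or dose from the existing baseline plan, and use it as a covariate in place of, or beside, total prescribed dose. The Intraoral PBMT section already has the team consult IMRT planning records to locate the gross tumour volume. Because the value is fixed by the baseline plan, it introduces no selection on post-treatment events.
3. **Analysis.** Keep intention to treat as primary. Prespecify the same non-inferiority analysis in participants with oral mucosa in the planned volume, and make a non-inferiority claim depend on a consistent result there. State in advance what counts as consistent.

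**Cost.** An amendment, one item read from each plan, somewhat slower recruitment, and a claim limited to at-risk patients. The at-risk analysis is also less precise among those already enrolled. If f were 25% throughout, about 24 × 0.75 = 18 per arm would remain; at SD 0.61, SE = 0.61 × √(2/18) = 0.203 and power is Φ(0.5/0.203 - 1.96) = Φ(0.50), about 69%. That loss is why this analysis should support the intention-to-treat result and not replace it. It shrinks as later patients enter under the amended criterion.

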## Clinical and treatment-related variables

Prophylactic PBMT will be administered thrice weekly during radiation therapy. Following institutional standards, all patients will undergo intensity-modulated radiation therapy (IMRT). The prescribed radiation regimen consists of total doses ranging from 60 to 70 Gy, delivered in 30 to 35 fractions of 2 Gy (200 cGy) per fraction, five days a week.

Following a pragmatic design, patients on concurrent chemotherapy will be included. As chemotherapy significantly impacts OM risk, it will be recorded and treated as a covariate in multivariable regression analyses to adjust for potential confounding on outcomes.

The standardized PBMT schedule was set for Monday, Wednesday, and Friday during all weeks of RT, ensuring a maximum interval of two days between sessions and coverage of at least three consecutive RT fractions. Three times per week (rather than daily) was based on the operational feasibility of the referral oncology service (patient flow and researcher availability), evidence from randomized clinical trials demonstrating that the efficacy of three-times-weekly PBMT protocols is comparable to daily frequency in SCC populations [22], and protocols approved by the MASCC/ISOO guidelines that include alternate frequencies [17].

### Protocols

#### Transcutaneous PBMT

TC PBMT utilizes the E-light IRL cluster (DMC^®^, São Carlos, SP, Brazil; hardware v. 2.0 101). Although the device incorporates dual-wavelength emitters (660 nm and 808 nm), only the 808 nm infrared (IR) emitters will be utilized for this study. These emitters consist of Aluminum Gallium Arsenide (AlGaAs) semiconductor diodes. The cluster comprises four IR emitters operating simultaneously, each with an output power of 100 mW. Each emitter will deliver 1 J/spot in 10 s. Beam characteristics are described as follows (Fig. 1):

Central Emitters (*n* = 2): beam area of 0.029 cm², resulting in an irradiance of 3.45 W/cm² and a fluence of 34.5 J/cm² (1 J per emitter).Lateral Emitters (*n* = 2): beam area of 0.233 cm², resulting in an irradiance of 0.43 W/cm² and a fluence of 4.3 J/cm² (1 J per emitter).

Detailed dosimetric parameters are summarized in Table 1.

The fluence values of central (34.5 J/cm²) and lateral emitters (4.3 J/cm²) refer to the skin-device interface; effective fluence at the oral mucosa will be considerably lower due to tissue attenuation, with a reported 10 to 50 fold reduction depending on total tissue thickness [27], which is acknowledged as a limitation of the TC protocol.

**Fig. 1 Fig1:**
[figure not shown]
Cluster device showing the four simultaneous emitters and dosimetric parameters of central (C1, C2) and lateral (L1, L2) emitters

Application Technique: Eight anatomical points will be irradiated in contact mode. Given the simultaneous firing of the four emitters, each application point receives a total of 4 J (1 J/ emitter), totaling 32 J/ session (80 s cumulative).

The anatomical mapping for TC PBMT includes (Fig. 2):

Buccinator muscles: eight points/side, right and left.External orbicularis oris: eight points (four superior and four inferior).Submandibular glands: four points (two/side, right and left).

The selection of 808 nm is supported by its positioning within the near-infrared optical therapeutic window (700–1100 nm), which minimizes absorption by hemoglobin and water, thereby maximizing tissue penetration depth [28]. Site-specific fluence estimates based on Monte Carlo simulations for 850 nm light spectrally close to the present device demonstrate considerable variation by anatomical site: 0.4–10.0 mW/cm² at the cheek, 2.4–35.5 mW/cm² at the mandible angle, and 5.6–36.3 mW/cm² at the lip, depending on total tissue thickness [27]. For the lateral tongue, irradiation is performed via submandibular application points, with light traversing skin, subcutaneous tissue, and muscular layers before reaching the target mucosa. The soft palate was not included among TC application points due to its anatomically unfavorable position for transcutaneous light delivery, which is acknowledged as a coverage limitation of the TC protocol.

**Fig. 2 Fig2:**
[figure not shown]
Transcutaneous application points: the orbicularis oris muscle, the floor of the mouth and left and right buccinator muscle

### Intraoral PBMT

IO PBMT will be administered using the Therapy EC device (DMC^®^, São Carlos, SP, Brazil). This system utilizes an Aluminum Gallium Indium Phosphide (AlGaInP) semiconductor diode laser featuring a single-emitter laser (0.098 cm²). The procedure will be performed in contact mode using a visible red wavelength of 660 nm.

The device operates at an output power of 100 mW, resulting in an irradiance of 1.02 W/cm². Each application point will receive 1 J of energy over a 10-second irradiation interval, corresponding to a fluence of 10.20 J/cm² (Table 1).

Application Technique: A 44-point protocol covers the buccal mucosa [29]. The anatomical distribution is defined as follows:

Buccal mucosa: 16 points (8/ side).Labial mucosa: 8 points (4 superior and 4 inferior).Buccal folds: 6 points (3/ side).Tongue: 9 points (4 on each lateral border and 1 on the tip).Soft palate: 3 points.Labial commissures: 2 points (1/ side).

Total energy is 44 J/ session, lasting 440 s (7 min and 20 s). The clinical mapping of these points is illustrated in Fig. 3.

Three calibrated examiners will perform all clinical assessments; however, blinding will not be feasible in this study due to the visually distinguishable nature of the two PBMT protocols.

For both TC and IO protocols, PBMT will not be applied directly to the gross tumor volume (GTV), as defined in the IMRT planning records available in the patient’s medical record. In cases where any predetermined application point coincides with the GTV, the point will be repositioned or omitted, and this decision will be recorded on the data collection form.

**Fig. 3 Fig3:**
[figure not shown]
Intraoral PBMT points application sites located in non-keratinized mucosal: superior and inferior oral, and left and right buccal mucosa, soft palate, floor of the mouth, left and right tongue borders

**Table 1 Tab1:** Parameters of intraoral and transcutaneous photobiomodulation

PARAMETER	INTRAORAL	TRANSCUTANEOUS
Wavelength (nm)	660	808
Laser type	AlGaInP diode laser	AlGaAs diode laser (4-emitter cluster)
Power per emitter (mW)	100	100
Total cluster power (mW)	–	400
Spot size (cm²)	0.098	Central emitters: 0.029 Lateral emitters: 0.233
Irradiance (W/cm²)	1.02	Central: 3.45 Lateral: 0.43
Energy per point (J)	1	1
Fluence (J/cm²)	10.20	Central: 34.5 Lateral: 4.3
Time per point (s)	10	10
Number of points per session	44	8 applications (4 emitters, 32 points)
Total energy per session (J)	44	32
Total irradiation time per session (s)	440	80
Application mode	Contact	Contact

